### Interventions

#### Interventions common to both arms

Trial participants will receive the infusion at the pain intravenous infusion unit at Toronto Western Hospital (Toronto, Ontario, Canada), under cardiorespiratory monitoring, supervised by an anesthesiologist. At the start of the infusion, all participants will receive IV midazolam 0.04 mg kg^−1^ (maximum 3 mg) and subsequently 0.01–0.02 mg kg^−1^ every hour to keep participants in a sedated but arousable state (Ramsay Sedation Scale score 3 or 4) [19] in an attempt to blind the participants and assessors to trial group allocation. Eight milligrams of ondansetron and 8 mg of dexamethasone will be administered to all participants to prevent nausea and vomiting, and 5000 units of heparin will be given subcutaneously to prevent thrombo-embolic events. All medications will be administered by a trained and board-certified anesthesiologist (Fig. 1).

**Fig. 1 Fig1:**
[figure not shown]
Flow diagram for the KetHead RCT

##### Intervention group

For individuals randomized to the IV Ketamine group, 1 mg. kg^−1^ bolus will be given. To deliver this dose, a volume of 0.1 mL.kg^−1^ will be administered from a syringe of 10 mL with 10 mg/mL of ketamine. This will be followed by an infusion of 1 mg. kg^−1^ .h^−1^ (ketamine diluted in saline to 2 mg. mL^−1^; so an infusion rate of 0.5 mL .kg^−1^. h^−1^) for 6 h.

##### Control group

For individuals randomized to the saline infusion group, an IV bolus of 0.9% saline (0.1 ml. kg^−1^) will be given. This is followed by an infusion of 0.5 mL. kg^−1^. h^−1^ of saline for 6 h. The volume of bolus and rate of the infusion will be the same as that of a ketamine infusion for the body weight to prevent unblinding of participants and assessors.

We will use an approved Health Canada-marketed version of ketamine hydrochloride for this trial. The trial medication will be prepared by appropriately qualified health personnel in order to ensure the integrity of the trial protocol and to maintain blinding. The pharmacist dispensing the trial medication will not be blinded but they will not interact with the trial participants at any stage. When a patient is randomized, the delegated clinical nurse will check the corresponding treatment number (as assigned through an opaque sequentially numbered allocation envelope) and provide a prescription to the pharmacist to dispense the trial medication. In the event a subject is randomized but never administered any trial medication, the treatment will not be reassigned. Trial medication preparations are subject-specific only and will not be administered to another patient.

Trial personnel will assess the patient and collect data throughout their enrollment in the trial.

During the trial, participants will be instructed to use a pain and migraine diary for the collection of data on migraine days, pain scores, and rescue pain medication during the first 84 days after the infusion.

Participants will be assessed for the collection of outcomes immediately after the infusion and during the first 84 days after the infusion.

Participants in both arms will wear an actigraphy device (Additional file 1: Appendix 1) to assess the quality and duration of sleep and activity for 1 week prior to the trial medication infusion (for collection of baseline data) and starting on the day of infusion for 1 month after the infusion to longitudinally assess the impact of the trial treatments on sleep and activity.

#### Modifications

Discontinuation of the trial procedure will occur at the request of the participant. Any participant who experiences a serious adverse event at any point will immediately discontinue participation in the trial. The timing and reason for the discontinuation of the trial will be recorded.

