### Statistical methods

The normality of the trial data will be assessed, means and standard deviation (or median and interquartile ranges, as appropriate) will be used to summarize continuous data, and frequencies and proportions will be used for categorical data. To compare data between the 2 groups, categorical outcomes will be analyzed with the chi-square test and continuous variables will be analyzed with independent *t*-tests (or Wilcoxon rank sum test). A baseline-adjusted ANCOVA model will be employed for all outcome variables of interest for which a baseline is recorded in the 28 days interval prior to treatment. In addition, for the primary outcome, an additional ANCOVA model will be employed adjusting for baseline headache days and the following variables that are strongly associated with this outcome: number of headache years, depression/anxiety, intensity of headache, and opioid intake. Estimates of differences in means (with 95% CI) at 28, 56, and 84 days will be provided for continuous outcomes. A Cox proportional hazards model will be built to investigate the effect on variables on the time to a specified event. Missing primary outcome data will not be imputed. A sensitivity analysis assuming the participants lost to follow-up showed no improvement (i.e., they had no change in headache frequency) will then be performed. Group comparisons will be performed in responders (defined as a reduction in pain by 3 or more headache days in 28 days from baseline at 28 days after the infusions) versus non-responders, participants on Botox/CGRP antagonist treatment versus none, comparison across different subtype of CDH, and baseline frequency and average intensity of headaches. An intention-to-treat analysis approach will be used. SAS Studio Edition will be used to conduct the analyses.

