### Safety/harms

Monitoring and reporting of adverse events will be conducted from the time of consent to trial entry until the end of the trial. Adverse events will be documented in the patient file and electronic case report form and reported to the UHN REB.

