### Criteria for subject withdrawal

Subjects have the right to withdraw from the trial at any time, without providing a reason. In the event that a subject decides to prematurely discontinue from the trial, they will be asked if they can still be contacted for further information. This will be documented accordingly. If the subject has already received the trial medication prior to withdrawal, the subject will be requested to be contacted for a safety follow-up visit.

When applicable, subjects should be informed of the circumstances under which their participation may be terminated by the investigator without their consent. The investigator may withdraw the subjects from the trial in the event of intercurrent illness, adverse events, lack of compliance, or at the request of the Institutional Review Board.

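### A serious adverse event at any point ends trial participation, although after a single infusion only follow-up remains to be stopped; this conflicts with the planned safety monitoring and the intention-to-treat analysis

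*Protocol article*

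**What the plan says.** The protocol article treats leaving the trial in several places.

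- **Modifications (under Interventions):** "Any participant who experiences a serious adverse event at any point will immediately discontinue participation in the trial". The next sentence says what is kept: "The timing and reason for the discontinuation of the trial will be recorded".
- **Control group (under Interventions), on data collection in general:** "Trial personnel will assess the patient and collect data throughout their enrollment in the trial".
- **Safety/harms:** "Monitoring and reporting of adverse events will be conducted from the time of consent to trial entry until the end of the trial". The Objectives also list adverse-effect assessments at 7, 28, 56 and 84 days.
- **Criteria for subject withdrawal:** "The investigator may withdraw the subjects from the trial in the event of intercurrent illness, adverse events, lack of compliance", or at the review board's request. The same section asks for a safety follow-up visit when a withdrawn subject has already received trial medication.
- **Statistical methods:** "An intention-to-treat analysis approach will be used"; "Missing primary outcome data will not be imputed"; and then "A sensitivity analysis assuming the participants lost to follow-up showed no improvement", meaning unchanged headache frequency.

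**The concern.** The only trial treatment is a bolus and one 6-hour infusion on day 0. Once it is over there is nothing left to discontinue except the diary, the visits and the adverse-effect assessments. The rule nevertheless covers any SAE, related or not, at any time. It ends participation in the trial, whereas the sentence before it speaks more narrowly of the trial procedure.

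Two things are at stake. First, a participant removed before day 28 has an incomplete primary outcome because the protocol ordered it. That loss is avoidable, it may be related to outcome, and no later analysis plan can recover data that were never collected. Second, the participants in whom later safety information matters most would miss the remaining scheduled assessments, in a 56-person trial that also sets out to judge safety.

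**Working it through.** **The plan's own figures.** Sample size section: difference 3 days, SD 3.8, two-sided alpha 0.05, 25 evaluable per arm, 10% dropout.

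- Standard error = 3.8 × √(2/25) = 1.075. Then 3/1.075 − 1.96 = 0.83, which gives power of 79.7% (normal approximation); the noncentral t gives 78.1%. The article says over 80%, so this reproduces closely.
- 25/0.9 = 27.8, rounded up to 28 per arm, as stated.

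The present point does not depend on the power figure. Only the arm size of 28 and the 3-day difference are used below.

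**The sections side by side.**

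1. Modifications ends participation; the Control group section ties data collection to enrollment in the trial. Together they imply that collection stops. This is an inference: no sentence says outright that the diary ends. But no sentence says that it continues, and only timing and reason are named as recorded.
2. Safety/harms promises monitoring to the end of the trial. A participant who left at an SAE on, say, day 10 would miss the day 28, 56 and 84 assessments.
3. Modifications is mandatory for an SAE; Criteria for subject withdrawal is discretionary for adverse events, a class that includes SAEs. Both cannot govern the same event.
4. Statistical methods analyses by intention to treat without imputing the primary outcome. Anyone removed before day 28 then has no complete count and would be left out of the main comparison.

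**Size of the effect on the primary outcome.** The article gives no SAE rate, so the following are assumptions: k ketamine participants are removed before day 28, none are removed on placebo, there is no other loss, and the removed participants' counts would have averaged D days above the mean M of the full ketamine arm. The mean of those remaining is

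(28M − k(M + D)) / (28 − k) = M − kD/(28 − k),

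so the complete-case mean looks better by kD/(28 − k).

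| k | D = 3 | D = 6 |
|---|---|---|
| 1 | 3/27 = 0.11 (4%) | 6/27 = 0.22 (7%) |
| 2 | 6/26 = 0.23 (8%) | 12/26 = 0.46 (15%) |
| 3 | 9/25 = 0.36 (12%) | 18/25 = 0.72 (24%) |

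Percentages are of the 3-day difference. If D were zero there would be no shift; if D were negative the shift would go against ketamine.

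**Cross-check.** Suppose the removed participants had no benefit and the others gained 3 days. The effect over all 28 would be 3 × (1 − k/28) = 2.89, 2.79 and 2.68 days for k = 1, 2, 3, while the complete-case analysis would still show 3.0. That is about 0.11 day per removed participant.

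**Power.** Losing 1, 2 or 3 ketamine participants beyond the planned dropout (25 − k against 25) takes power from 79.7% to 78.9%, 78.0% and 77.1%. That cost is small; the issue is bias and lost safety data.

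**The case against.** The other side has real points.

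- **The sensitivity analysis.** If participants removed for an SAE count as lost to follow-up, the plan scores them as unchanged, which tests the feared bias. This stands as mitigation. It is not a substitute for observed data: it is secondary, it concerns headache frequency only, and it cannot represent someone who got worse.
- **Safety data do not simply stop.** A reader might infer that they do. The SAE itself is recorded and reported, a safety visit is requested after withdrawal, and follow-up care is offered for harm. What is at risk is the later scheduled assessments. The request for further contact is, moreover, worded for subjects who choose to leave.
- **Arm imbalance is not shown.** A reader might infer it from the Discussion, which calls ketamine's adverse effects common. The same section describes most as mild and resolving, and the rule is triggered only by serious events. Unrelated SAEs would be expected in both arms.
- **Bias in ketamine's favour is not shown either.** Nothing in the article says that an SAE predicts more headache days; that direction comes from taking D as positive.
- **Intention to treat is not made impossible.** Such an analysis can tolerate some missing outcomes with a sensitivity analysis. The conflict is that the protocol itself creates avoidable missingness.
- **Timing.** An SAE after day 28 leaves the primary outcome untouched and costs only later outcomes and safety data.

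None of this reconciles the sections with one another.

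**Conclusion.** The concern holds as a conflict in the text that should be fixed. For an SAE after the infusion, the rule as written can only end follow-up. That is at odds with monitoring to the end of the trial, with the discretionary withdrawal wording and with an unimputed intention-to-treat analysis. That outcome data would be lost is inferred from two sections read together.

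Under the stated assumptions (1 to 3 removals before day 28, all on ketamine, counts 3 to 6 days worse than the arm mean), the shift is 0.11 to 0.72 days. The upper end needs about 11% of the arm (3/28) to be removed, each 1.6 SD (6/3.8) worse than the mean, so it should not be read as the expected size. The documents do not support a claim that the trial is biased towards ketamine. They support the claim that it would lose information it could easily keep.

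**What to change.** Reconcile Modifications, Statistical methods, Safety/harms and Criteria for subject withdrawal by separating two decisions:

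1. **Stopping the trial infusion.** This is a clinical matter for the investigators to define; no position is taken here. The mandatory and discretionary wordings must be made to agree.
2. **Stopping follow-up.** State that participants with an SAE, a stopped infusion or non-compliance stay in the already scheduled diary, the day 28, 56 and 84 assessments and adverse event follow-up unless they withdraw consent, and are analysed as randomised.

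The sensitivity analysis can stay for data that are still missing. The cost is protocol wording and one line in the consent form. No visits are added and the sample size does not change.

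### A serious adverse event at any time ends trial participation, although after the single infusion there is only follow-up left to stop

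*Protocol article*

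**What the plan says.** The Modifications paragraph of the protocol article has two rules with different objects. The one on the procedure reads "Discontinuation of the trial procedure will occur at the request of the participant". The one on serious adverse events (SAEs) reads "Any participant who experiences a serious adverse event at any point will immediately discontinue participation in the trial". The SAE rule is mandatory, has no time limit and does not ask whether the event is related to treatment. The paragraph adds that the timing and reason will be recorded.

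Other sections bear on it:

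- **Follow-up** (Control group): "Participants will be assessed for the collection of outcomes immediately after the infusion and during the first 84 days after the infusion". The Participant timeline sets visits at days 28, 56 and 84, in person or virtual.
- **Safety** (Objectives; Safety/harms): adverse effects are to be assessed at days 7, 28, 56 and 84, and adverse events are monitored from consent to the end of the trial.
- **Analysis** (Statistical methods): "An intention-to-treat analysis approach will be used" and "Missing primary outcome data will not be imputed". A sensitivity analysis assumes no change in headache frequency for participants lost to follow-up.
- **Withdrawal** (Criteria for subject withdrawal): "The investigator may withdraw the subjects from the trial in the event of intercurrent illness, adverse events, lack of compliance", among other reasons. A participant who chooses to leave is asked about further contact ("they will be asked if they can still be contacted for further information"). For anyone already dosed before withdrawal, "the subject will be requested to be contacted for a safety follow-up visit".

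**The concern.** Stopping treatment and stopping observation are separate decisions. With a single 6-hour infusion, a stopping rule for SAEs can limit exposure only before or during that infusion. Afterwards, the only thing left to discontinue is data collection. An unrelated hospital admission on day 10 would, on the wording, end the diary and all three visits for someone who could still be followed.

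Two things are at stake. The first is the primary comparison. An SAE before day 28 leaves the headache-day count incomplete, for a post-randomisation reason that may depend on the arm, and the main analysis does not impute it. The second is safety. Participants who have had an SAE are those whose later course matters most, and the rule would cut short their planned adverse-effect assessments.

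**Working it through.** **The plan's own figure.** The rule carries no number. The sample-size section is needed only to check power. Inputs there: difference 3 headache days, SD 3.8, two-sided alpha 0.05, 25 per group, 10% drop-out.

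- Normal approximation: 2 × (1.96 + 0.842)² × 3.8² / 3² = 25.2, so 26 per group (stated: 25).
- Power at 25 per group: 79.7% (normal) or 78.1% (noncentral t). This is close to the stated figure of over 80%, though slightly below it.
- Drop-out: 25 / 0.9 = 27.8, so 28 per arm, as stated.

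Nothing below depends on the small gap at 25 per group.

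**What the rule removes for one participant, read literally.** Days lost after an SAE on day d = 84 − d.

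| SAE on day | Days lost of 84 | Visits lost | Primary count (days 1–28) |
|---|---|---|---|
| 1 | 83 (99%) | 28, 56, 84 | incomplete |
| 14 | 70 (83%) | 28, 56, 84 | incomplete |
| 40 | 44 (52%) | 56, 84 | complete |

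These percentages describe one participant's calendar, not the effect on the trial.

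**How many participants.** The documents give no SAE rate. Assuming a risk of 1% to 5% up to day 28: 28 × 0.01 = 0.28 and 28 × 0.05 = 1.4 per arm.

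**Effect on the primary estimate.** Suppose each lost participant would have had D more headache days than those remaining in the same arm, with D an assumption. The complete-case difference then departs from the all-randomised difference by

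D × (k_ketamine − k_placebo) / 28,

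where k is the number lost in each arm.

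| D (days) | Lost, ketamine v placebo | Shift (days) |
|---|---|---|
| 1 | 1 v 0 | 0.04 |
| 3 | 1 v 0 | 0.11 |
| 3 | 2 v 0 | 0.21 |
| 3 | 3 v 0 | 0.32 |
| 3 | 1 v 1 | 0 |

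For scale, the standard error of the difference at 28 per arm is 3.8 × √(2/28) = 1.02 days, so the 0.11-day shift is about a tenth of it.

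**Effect on power** (noncentral t, difference 3, SD 3.8): 82.7% at 28 v 28, 82.0% at 27 v 28, 81.2% at 27 v 27.

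**What existing provisions recover.** The safety visit is a request for one contact and does not secure diary or scheduled outcome data. The no-improvement analysis can cover the primary outcome if these participants are counted as lost to follow-up. It then substitutes an assumption for data that could have been collected, and it concerns headache frequency only.

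**The case against.** The strongest case for the plan is that the sentence is loosely worded and that the rest of the document contains the damage. It sits under Interventions, straight after a sentence on stopping the procedure, so it may have been meant to stop treatment only. The article condenses a fuller protocol (version 3.0), which may set out follow-up after an SAE. The safety visit depends only on having been dosed, so it also reaches a participant withdrawn because of an SAE. Care for harm is provided, and a sensitivity analysis for losses exists.

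Much of this stands. It lowers confidence about what sites would do and softens the loss of safety data. It does not change the sentence, which moves from the procedure to participation in the trial and uses mandatory language.

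A reader might also infer that the rule flatly contradicts other sections. The documents do not support that:

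- The withdrawal section's discretion covers adverse events in general. A mandatory rule for the serious subset can stand beside it, and a site can obey both.
- Intention to treat can be declared with missing outcomes. The rule makes it harder to carry out but does not negate it.
- The adverse-effect time points and the monitoring period are statements about the trial as a whole, ordinarily subject to withdrawals. The rule undercuts their purpose without contradicting them.

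For an SAE before or during the infusion, cancelling or stopping the infusion is sensible.

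**Conclusion.** The point holds as a badly fixed rule. Followed as written, it creates avoidable missing outcome data and shortens safety follow-up after an SAE, with no exposure left to prevent once the infusion is over. It is in tension with the analysis approach and the safety objective. It should be fixed, with medium confidence, because a looser reading is possible.

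The size is modest. On an assumed 1% to 5% risk by day 28, about 0.3 to 1.4 participants per arm would be affected. One unbalanced loss shifts the primary estimate by 0.04 to 0.11 days if D is 1 to 3, and balanced losses with equal D shift it by nothing. Both the risk and D are assumptions. A reader might infer that the rule threatens the power or the conclusion of the primary analysis; the figures do not support that. The case rests on the selective and unnecessary nature of the loss, and on its falling on the participants most informative for safety.

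**What to change.** Reword the SAE sentence under Modifications to say that:

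- an SAE stops a running infusion, or cancels one not yet given, as clinically indicated;
- the participant stays in the diary, the day 28, 56 and 84 visits (virtual if needed) and adverse-event follow-up to day 84, unless consent is withdrawn;
- the participant is analysed as randomised.

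Add a matching line under Criteria for subject withdrawal: investigator withdrawal for adverse events means withdrawal from treatment, with the safety visit as the minimum for those who decline further follow-up. Keep the no-improvement sensitivity analysis for participants who are truly lost.

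The cost is one reworded sentence, one added line and a few extra follow-up contacts. No design figure changes.

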#### Concomitant care

There will be no restrictions or changes to the baseline home medication, but participants will be advised to avoid the introduction of new analgesic agents in the post-infusion period.

#### Rescue medication and risk management

Any other pain medications provided during the infusion are considered rescue therapy. Participants will be given symptomatic treatment, and standard care will be provided. If any side effects or complications arise due to the use of trial medications, emergency unblinding will only occur when knowledge of the intervention is essential for medical care as determined by the principal investigator. In the event of emergency unblinding of one or more research team members, the timing, reason, and personnel involved will be recorded in the case record form (CRF), and blinding will be maintained for as many other trial personnel as possible.

